**Signatures**

|  |  |  |  |
| --- | --- | --- | --- |
| Chief Investigator | Signature |  | Date |
|  |  |  |  |
|  |  |  |  |
|  |  |  |  |
|  |  |  |  |
| Trial Statistician | Signature |  | Date |
|  |  |  |  |
|  |  |  |  |
|  |  |  |  |
|  |  |  |  |
|  |  |  |  |
|  |  |  |  |
|  |  |  |  |
|  |  |  |  |
|  |  |  |  |

list of abbreviations

| AE | Adverse event |
| --- | --- |
| BMI | Body Mass Index |
| CRF | Case report form |
| CTCAE | Common Terminology Criteria for Adverse Events |
| E | Estradiol |
| EC | Ethics Committee |
| ECTU | Edinburgh Clinical Trials Unit |
| ECM | Extracellular Matrix |
| eGFR | Estimated Glomerular Filtration Rate |
| FSH | Follicle stimulating hormone |
| GnRH | Gonadotropin releasing hormone |
| GP | General Practitioner |
| HMB | Heavy menstrual bleeding |
| ICH GCP | International Conference on Harmonization of Good Clinical Practice |
| LH | Luteinizing hormone |
| MRI | Magnetic Resonance Imaging |
| MTI | Magnetization transfer imaging |
| MTR | Magnetization transfer ratio |
| P | Progesterone |
| SAE | Serious adverse event |
| SOP | Standard Operating Procedure |
| TAS | Transabdominal Scan |
| TMRC | Translational Medicine Research Collaboration |
| TMRI | Translational Medicine Research Institute |
| TVU | Transvaginal ultrasound |
| UAE | Uterine artery embolisation |
| ULN | Upper Limit of Normal |
| USS | Ultrasound Scan |

summary

Uterine fibroids (leiomyomas) are present in up to 80% of women of reproductive age. Associated heavy menstrual bleeding is frequently an indication for surgery. The only medical therapies for treating uterine fibroids are GnRH agonists. Non-invasive biomarkers to monitor clinical response of these agents on reduction of fibroid size and reduction in bleeding are needed. This proposal will evaluate the biomarker potential of contrast-enhanced magnetic resonance (MR) imaging in women with fibroids treated with standard therapies that reduce menstrual bleeding and fibroid/uterine size prior to hysterectomy.

# **INTRODUCTION**

## **1.1 BACKGROUND**

Complaints of excessive blood loss impose a detrimental impact on quality of life for healthy women1. Annually in the UK 3.5 million workdays are lost2 and treatment costs for menstrual complaints exceed £65m. Heavy menstrual bleeding (HMB; menorrhagia) is by far the most common complaint in women with symptomatic uterine fibroids (also termed leiomyomas), and represents the major indication for surgical intervention (hysterectomy).

Fibroids may be present in as many as 80% of women of reproductive age. One in 4 Caucasian women report clinically significant symptoms attributable to the presence of fibroids. Prevalence peaks in the perimenopausal years. Obesity and an early menarche are known risk factors, likely due to the increased lifetime exposure to oestrogen3. The mechanism of HMB in women with fibroids is not understood.

To date there are no approved medical treatments for long-term management of women with symptomatic fibroids.

Current treatments for fibroids are surgical or invasive in nature. Surgical removal (myomectomy) and hysterectomy are mainstays of management. Uterine artery embolisation (UAE) was introduced ten years ago as an alternative to hysterectomy for the surgical management of fibroids. The efficacy of UAE as an alternative therapy to surgery for uterine fibroids has recently been demonstrated to require longer-term follow-up4.

GnRH-analogues are used for medical treatment of symptomatic uterine fibroids pre-surgery. After 3-6 months of treatment, the resultant hypo-oestrogenic state results in an average 20-50% decrease in uterine and fibroid size5. It is assumed that it is the hypoestrogenism that causes shrinkage of fibroids; however addition of tamoxifen actually increases fibroid growth6. Much of the shrinkage occurs in the first 2 weeks when the women are not hypoestrogenic. The immediate suppression of the pituitary achieved with GnRH antagonists, with no initial stimulatory effect is the main advantage over the GnRH agonists. GnRH antagonists have been developed with acceptable pharmacokinetic and safety profiles7 and use proposed for management of fibroids.

There is unmet need for a pharmacologic agent able to reduce excessive bleeding and other symptoms associated with increased uterine volume, which could prevent or significantly delay surgery without causing significant unwanted hypoestrogenic side effects and allow preservation of fertility.

This study involves the use of non-invasive MR imaging of uterine morphology and vasculature and will provide invaluable information as to whether such techniques could be used as an efficacy biomarker in clinical trials involving novel potential therapeutic agents for medical treatment of uterine fibroids. The development of such a biomarker will facilitate the assessment of drugs in development for uterine fibroid therapy and the study of uterine pathologies in general.

**Novel magnetic resonance imaging of uterine fibroids (leiomyomas) to inform on modulation of vasculature and fibroid morphology**

MR imaging is a useful and acceptable tool for assessing the presence, location and size of uterine leiomyomas *in vivo*8,9,10 The technology is non-invasive and does not involve ionizing radiation. Furthermore, MRI technologies are being developed to be able to resolve tissue detail to near cellular level11.

Improvement in MRI techniques, such as that provided by 3T imaging, could allow characterisation of change in uterine and fibroid volume, vasculature and structure after pharmacologic interventions (e.g. administration of GnRH-agonists9), with a better resolution compared to other imaging methods, such as Doppler US. Additional information may also be provided by using diffusion-weighted imaging (DWI)12 and magnetisation transfer imaging11.

Our goal is to test the validity of novel MR imaging modalities, such as dynamic contrast and magnetization transfer imaging as non-invasive biomarkers of volumetric, vascular, and structural dynamic changes in the disease progression after a medical intervention. We have previously used the technique of dynamic contrast imaging at a number of time points to measure perfusion and permeability parameters in brain tumours following dexamethasone treatment13. We have also used magnetization transfer imaging to look at structural changes occurring in periventricular white matter lesions in normal ageing11.

Examination of the macroscopic and microscopic features of hysterectomy specimens will allow correlation with the imaging results.

## **1.2 RATIONALE FOR STUDY**

The purpose of this study is to investigate and validate the potential use of structural, dynamic contrast and magnetization transfer MR imaging as a non-invasive biomarker for monitoring responses to medical interventions aimed at reduction of excessive menstrual bleeding and decrease in uterine/ fibroid volume.

Such MR imaging strategies should provide a method to visualize and quantify changes in:

1. uterus and fibroid volume;
2. uterine vascular density and perfusion;
3. vasculature and extracellular matrix content of fibroids -

in women with fibroids administered a gonadotrophin-releasing hormone agonist (GnRH-a), either alone or with initial administration of a GnRH antagonist, for adjunct therapy to reduce uterine bleeding prior to hysterectomy.

The proposed study design will also provide important mechanistic information on whether the reduction in blood flow of uterine/ fibroid vasculature and shrinkage of fibroids is dependent upon subjects being hypoestrogenic.

Comparisons of novel magnetic resonance imaging data of the fibroid uterus, pre- and post GnRHa, GnRH antagonist, with a comparative “control” group of women who receive no therapeutic intervention pre-hysterectomy, will be made.

We will employ (1) routine ultrasound and colour Doppler imaging techniques; (2) use MR imaging and explore a novel “pre-clinical” opportunity to examine ex-vivo 7T imaging and correlate imaging data with the histo/morphology of uterine specimens; and (3) undertake histo-morphology of the uterus removed at hysterectomy. We will evaluate whether imaging with MR is applicable for the study of modulation of morphology and cellular arrangements of tissue and vascular structures in the uterus, thereby informing mechanism of action of therapies.

Specifically, we will investigate the use of dynamic contrast imaging using standard contrast agents to characterize changes in fibroid perfusion and permeability after treatment. For example, perfusion parameters, such as time to peak, mean transit time etc. can be determined from the first pass of the bolus of contrast agent, while signal-time curves give information on tissue permeability. Finally, we shall also investigate the use of magnetization transfer imaging (MTI). This imaging modality provides an index, the magnetization transfer ratio (MTR), which measures the efficiency of the magnetization exchange between the relatively free water protons inside tissue and those bound to protein macromolecules in cellular membranes. MTR may therefore help differentiate fibrous from normal tissue and indicate pathological change in fibroid structure after treatment.

MTI has previously been used in brain imaging13. Its use in uterine imaging will be completely novel.

The evaluation of ex-vivo uteri has not been previously reported. This methodology could theoretically give almost cellular or histo-pathological level detail of pathology. This is relevant as spatial resolution increases with increasing field strength of MRI units, 3 Tesla (3T) will soon be the clinical standard. As MRI is non-ionising it can be used as a repeated study to assess early, efficacy of success of an intervention. The proposed ex vivo study will enhance the interpretation of correlations between 1.5/3T MR imaging data and the histo-morphology of the uterus/ fibroid(s). If longer term medical treatment strategies are to become a mainstay of clinical management of symptomatic fibroids it will be essential to have confidence in MR as a biomarker of response to treatment and resolution/ progression of disease. Thus far it has not been possible to determine when a fibroid exhibits concerning atypical features with either ultrasound or standard MR.

Importantly the proposal will permit investigation of the mechanism of action of the above therapeutic interventions. It is assumed that much of the decline in volume of fibroids following treatment with GnRH agonist is due to decline in oestrogen. In fact during the first 10-12 days there is an increase in oestrogen due to “flare”. In contrast following GnRH antagonist there is an immediate drop in oestrogen. This proposal provides an opportunity to investigate the role of hypoestrogenism as an important component of the therapeutic effect of these compounds. By taking serial imaging measurements pre-treatment, at 14+/- 3 days, 28+/- 3 days after starting treatment and up to 10 days before hysterectomy the dynamics of the changes in size, blood flow, perfusion and extracellular matrix can be studied.

# **STUDY OBJECTIVES**

## **2.1 OBJECTIVES**

### **2.1.1 Primary Objective**

##### To establish the feasibility and reproducibility of novel MR imaging techniques in the evaluation of treatment response in women with uterine leiomyomas (fibroids).

### **2.1.2 Secondary Objectives**

To provide mechanistic information on whether the reduction in blood flow of uterine/fibroid vasculature in shrinkage fibroids is dependent upon subjects being hypoestrogenic.

## **2.2 ENDPOINTS**

### **2.2.1 Primary Endpoint**

Feasibility and reproducibility of use of structural, dynamic contrast and magnetization transfer (MTI) MR imaging to visualize and quantify changes in:

1. Uterus and fibroid volume

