### **2.2.2 Secondary Endpoints**

1. Uterine vascular perfusion

1. Vasculature and extracellular matrix (ECM content of fibroids)

3. Whether (a) reduction of blood flow of uterine and fibroid vasculature and (b) shrinkage of fibroid depends upon subject being hypoestrogenic.

NB. The study aims to establish feasibility and reproduce ability of novel MR imaging techniques in the evaluation of treatment response in women with uterine fibroids. Hence there is not an efficacy measurement required for any of the drug treatment options.

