##### Clinical MR imaging will be performed. Patients will be examined on four occasions:

##### (1) before commencing GnRH agonist, GnRH antagonist therapy (visit 1);

##### (2) after 14 days+/- 3 days (visit 2);

##### (3) after 28 days +/- 3 days (visit 3);

##### (4) within 10 days prior to hysterectomy(visit 4)

Pre- and post GnRH agonist / GnRH antagonist treatment and control subjects will undergo breath-hold fast-spin-echo T2-weighted imaging acquired in planes oblique to the uterus, magnetization transfer, contrast-enhanced T1-volume scans and dynamic contrast imaging using a phased array torso coil on MR scanner.

Dynamic contrast imaging will use T1-weighted SPGR scans acquired at a number of time points after injection of gadolinium, e.g.  = 0, 30, 60, 90, 120 180, 240 and 300 seconds (Have practical limits in that patients usually become restless after about 30-40 minutes in MRI). Development work will be required to determine the optimum number and temporal resolution for this imaging to allow analysis of fibroid perfusion and permeability. Subjects will be carefully positioned so that the scan locations are as close as possible between pre- and post-treatment examinations. The use of image registration methods, such as FLIRT (www.fmrib.ox.ac.uk/fsl), to allow further fine alignment of imaging data will be investigated.

Uterus and enhancing and non-enhancing fibroid volumes pre- and post treatment will be determined from the T2- and T1-weighted structural scans using ANALYZE (Mayo Foundation, Rochester, MN, USA). Reduction in uterus and fibroid volumes will be determined as 100  (Volpre – Volpost)/Volpre.

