Uterine and fibroid vascular density will be determined from signal-time curves generated from the dynamic contrast imaging data. Following the protocol described by Jha et al. (2000)10, regions-of-interest (ROI) will be placed over fibroids and a control region, for example myometrium, and signal-time curves produced. The ratio of fibroid to myometrrium signal intensity will then be calculated for each of the time points , and the maximum value determined. This maximum ratio value will then be used to determine the effect of treatment on fibroid vascularity from the relation 100  (Ratiopre – Ratiopost)/Ratiopre. The application of image analysis protocols developed in the SFC Brain Imaging Centre, University of Edinburgh, to measure perfusion and permeability parameters from signal-time curves in brain tumours, will also be investigated in fibroids13.

Finally, we will investigate whether magnetisation transfer MRI (MTI) can provide a non-invasive biomarker to measure the clinical response of fibroids to treatment. This imaging modality provides an index, the magnetization transfer ratio (MTR), which measures the efficiency of the magnetization exchange between the relatively free water protons inside tissue and those bound to protein macromolecules in cellular membranes. We hypothesise that any pathological change in fibroid structure that involves alterations to cellular membrane macromolecules will change MTR and thus differentiate fibrous from normal tissue. We have previously used this technique to investigate the effects of ageing on the brain’s white matter11.

Development work will be required to determine the optimum imaging sequence parameters to provide MTI contrast in the uterus.

The examination of the uterus will include examination in the Preclinical Magnetic Resonance Imaging Unit (situated in the University of Edinburgh, Chancellors Building, at Little France site) using a 7T scanner. The inner diameter of the coil is 15cm thus able to accommodate the uterus once removed at hysterectomy. High resolution scans (T1W, T2W and MTI) will be carried out for comparison with histology.

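### The primary endpoint names three MR techniques but lists only volume, so dynamic contrast and magnetization transfer imaging have no primary read-out

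*Protocol*

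**What the plan says.** The primary objective (2.1.1) is "To establish the feasibility and reproducibility of novel MR imaging techniques in the evaluation of treatment response in women with uterine leiomyomas (fibroids"). The background (1.1) gives dynamic contrast and magnetization transfer imaging as its examples of novel modalities, and the rationale (1.2) describes MTI of the uterus as wholly new.

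The primary endpoint (2.2.1) is "Feasibility and reproducibility of use of structural, dynamic contrast and magnetization transfer (MTI) MR imaging to visualize and quantify changes in" a one-item list: "Uterus and fibroid volume". The secondary endpoints (2.2.2) begin with "Uterine vascular perfusion", followed by fibroid vasculature and extracellular matrix, and then the dependence of response on low oestrogen.

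Section 7.2.3 gives each technique a different output. Uterine and fibroid volumes "will be determined from the T2- and T1-weighted structural scans using ANALYZE". Dynamic contrast imaging gives signal-time curves, from which the maximum ratio of fibroid to reference-tissue (for example myometrial) signal is taken. Of MTI it says: "This imaging modality provides an index, the magnetization transfer ratio (MTR").

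Section 9.2 names two primary analyses: uterine volume before hysterectomy, treated against control, and a Bland-Altman comparison of MR with ultrasound. Perfusion is to be analysed similarly as a secondary matter.

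**The concern.** The objective and the endpoint do not match. The objective concerns whether novel MR techniques are feasible and reproducible. The endpoint repeats that aim and names the techniques, but the only quantity it counts is one that 7.2.3 obtains from structural scans.

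This looks like a slip in drafting. Section 1.2 introduces three targets with nearly the same lead-in: volume, vascular density and perfusion, and "vasculature and extracellular matrix content of fibroids". In section 2.2 the lead-in and all three techniques stay under the primary heading, while the second and third targets move to the secondary list.

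At stake is whether the trial answers its stated main question. The primary endpoint could be reported as met from volumetry, whatever happened with dynamic contrast or MTI. Section 7.2.3 says that both still need development work, so their feasibility is the more open question.

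**Working it through.** **Step 1. Match each technique to its read-out and its analysis.**

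| Technique named in 2.2.1 | Read-out in 7.2.3 | Listed in 2.2.1? | Primary analysis in 9.2? |
|---|---|---|---|
| Structural | Uterine and fibroid volume | Yes | Yes, uterine volume by group |
| Dynamic contrast | Signal-time curves, maximum signal ratio, perfusion and permeability | No | None clear; perfusion is secondary |
| MTI | MTR | No | None; no MTR analysis is named at any level |

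Two of the three techniques have no primary quantity.

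**Step 2. Ask whether the Bland-Altman analysis fills the gap.** Section 9.2 does not say which quantity is compared. Agreement needs the same quantity from both methods. Ultrasound gives ellipsoid volumes (7.2.1) and the resistance and pulsatility indices of the uterine arteries (7.2.2). MTR has no ultrasound counterpart, and those indices are not on the scale of a fibroid signal ratio. In practice the comparison works for volume.

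**Step 3. Check what section 9.1 was sized on.**
- Inputs: 10 per group, difference in volume change 160 cm³, SD 120 cm³, 5% level (two-sided assumed).
- Noncentrality = 160 / (120 × √(2/10)) = 160 / 53.7 = 2.98 on 18 degrees of freedom. The exact t-test power is 80.5%, against 80% stated.
- Half-width of the 95% interval for a limit of agreement, n = 30: 1.96 × √(3/30) = 0.62 SD, against 0.6 stated.

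Both figures reproduce. The first is for volume and the second names no quantity. Neither is expressed for the signal ratio or for MTR.

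**Step 4. See what the design can supply for the other two techniques.**
- *Feasibility.* Scheduled in-vivo scans in the main study: 30 women × 4 visits = 120 at most. The Appendix 4 chart for Group 1 lists no cannulation or gadolinium at Visit 2, whereas the charts for Group 2 and the control group do. As charted, contrast scans number 10 × 3 + 10 × 4 + 10 × 4 = 110.
- *Reproducibility.* Section 3.1.2 specifies one record per patient per measurement at each time-point, and no repeat scan or second read is described. Pilot Group C (up to 5 women) has two in-vivo scans at one visit, but at 1.5T and 3T, so these are not repeats of one measurement. What remains is between-visit variation in untreated controls: up to 10 women × 4 scans, hence 10 × (4 − 1) = 30 within-woman degrees of freedom.
- *Precision of that estimate.* If all scans are usable and errors are independent and normal, the 95% interval for the within-woman SD runs from √(30/46.98) = 0.80 to √(30/16.79) = 1.34 times the estimate (chi-square quantiles on 30 degrees of freedom). Missing scans widen it.

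**The case against.** The strongest reply is that volumetry belongs to the novel work. Section 3.1 speaks of refining novel volumetric evaluation in the pilot and counts structural scanning within the novel 1.5T package, and 7.2.3 lists fibroid volume among what the novel strategies characterise. This stands. A reader might infer that the trial could succeed on established MR alone, citing 1.1: "MR imaging is a useful and acceptable tool for assessing the presence, location and size of uterine leiomyomas". The documents do not support that, because this sentence is about presence, location and size, whereas the endpoint is about change.

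A reader might also infer that the trial would say nothing about dynamic contrast or MTI. That is too strong. Perfusion and matrix are secondary endpoints, image quality is to be explored, and 7T scans including MTI are compared with histology. The first two secondary items can even be read as completing the lead-in of 2.2.1, and the note under 2.2.2 repeats the feasibility aim. But the techniques named in the primary objective would then still be assessed only at secondary rank.

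Nor can one argue that gadolinium serves only the secondary measures. Section 7.2.3 includes contrast-enhanced T1 volume scans and separates enhancing from non-enhancing fibroid volume, and nothing says that MTI needs contrast.

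Finally, ranking volume first is defensible in a small hypothesis-generating study while the other sequences are in development. That supports leaving the power statement on volume. It does not explain an endpoint that names techniques for which it lists no measure.

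**Conclusion.** The mismatch is real, and it is one of definition. Dynamic contrast and MTI are named in the primary endpoint but have no read-out there and no clear primary analysis; MTR has no named analysis anywhere in 9.2. The primary endpoint could therefore be met without two of its three techniques, although the primary objective depends on them.

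The size is limited. Volumetry is itself presented as novel, the other quantities are kept at secondary rank, and neither figure in 9.1 changes. The conclusion rests on reading 7.2.3 as the definition of where each quantity comes from, and on its separate listing of contrast-enhanced T1 volume scans and dynamic contrast imaging.

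A statistical analysis plan should implement the endpoint that the protocol fixes, so the correction belongs in the protocol.

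**What to change.** - **2.2.1:** pair structural MR with uterine and fibroid volume, dynamic contrast with the maximum fibroid-to-myometrium signal ratio, and MTI with MTR.
- **9.2:** for the last two, report descriptively with confidence intervals (a) feasibility, as the proportion of scheduled scans that give an analysable read-out, and (b) between-visit within-woman variability in the untreated control group, up to four scans each. Present (b) as an upper bound on measurement error, because it includes menstrual-cycle variation. Do not claim same-session or reader reproducibility; that would need repeat scans or second reads, which 3.1.2 does not provide.
- **2.2.2:** keep the treatment effects on perfusion and matrix, and the hypo-oestrogenism question.
- **9.1:** leave the power statement on volume. The added parts are descriptive and spend no alpha.
- **Appendix 4:** reconcile the Group 1 Visit 2 entry with the Group 2 and control charts, so that the denominator for dynamic contrast feasibility (110 or 120) is known. Also reconcile the control chart, which times Visit 3 from Visit 2, with 3.1.2, which times it from the start of treatment, because the scan interval affects (b).

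The cost is rewording two sections and reconciling the charts, with no new visits. The downside is three descriptive primary parts instead of one, and repeatability estimates from about 10 controls that are imprecise: roughly 20% below to 34% above the estimated SD at best.
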